### Intervention

#### Pay-It-Forward Group

The research assistants at the vaccination clinics will use the PPSV-23 vaccination leaflet (Multimedia Appendix 1) to introduce participants in the pay-it-forward group to *S*
*pneumoniae*, the PPSV-23 vaccination, and its benefits. Subsequently, they will use the pay-it-forward program leaflet (Multimedia Appendix 2) to explain the purpose of the program, access to the PPSV-23 vaccination subsidy (US $20.7), and the opportunities to donate and write a postcard encouraging subsequent pay-it-forward recipients to receive the PPSV-23. The participants in this group will be informed of the standard cost of the PPSV-23 vaccination (US $29.5-$30) and the donations made by previous pay-it-forward recipients, as well as the handwritten postcards containing encouraging messages for the PPSV-23 vaccination. After watching the PPSV-23 promotional video, the participants will be surveyed by a research assistant using questionnaire A. They will be asked whether they are willing to be vaccinated and whether they are willing to make a donation or write a postcard with a message to encourage subsequent pay-it-forward recipients to become vaccinated with PPSV-23. The participants may donate at the vaccination clinics or online using their enrolled number (ie, the envelope number). They will also be informed that their decision to donate and the amount donated will not affect their eligibility for the vaccine subsidy and access to PPSV-23. The participants who are willing to be vaccinated will be evaluated for vaccination eligibility and scheduled for an appointment. The donations received will be used to support subsequent pay-it-forward recipients, and the amount and use of donations will be regularly updated on the official WeChat account. The CHWs will conduct follow-up surveys using questionnaire B and questionnaire C during the second and fourth weeks after enrollment. Each participant will receive 100 RMB (US $13.8) for completing the 3 surveys. The intervention fidelity will be monitored using a standardized fidelity checklist (Multimedia Appendix 3).

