### Randomization

This study will use block randomization to ensure balance between the intervention and control groups (block size=4). First, random sequences will be generated by computer from random seeds using SPSS software (version 25.0; IBM Corp). Each set of 4 random numbers will be grouped as a block and numbered in the order of generation. Subsequently, the random numbers within each block will be arranged in ascending order. The 2 smallest numbers will be assigned to the standard-of-care arm, and the 2 largest will be assigned to the pay-it-forward arm. Afterward, the study designer will write the corresponding numbers on the surface of opaque envelopes, insert the intervention material and group assignment information, and seal them. The participants will receive the envelopes corresponding to their assigned numbers and proceed with participation in the study.

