#### Standard-of-Care Group

The participants in this group will also receive the same PPSV-23 vaccination leaflet, a promotional video, and a questionnaire (not including questions on pay-it-forward) similar to that provided to the pay-it-forward group. They will also be informed of the standard cost of the PPSV-23 vaccination (US $29.5-$30). After watching the PPSV-23 promotional video, the participants will be surveyed by a research assistant using questionnaire A and informed that they will need to pay for the vaccination at the standard market price. Participants who are willing to be vaccinated will be assessed for eligibility and scheduled for an appointment for vaccination. The CHW will also follow up with the participants in the second and fourth weeks after enrollment. The participants will receive 100 RMB (US $13.8) for completing the 3 surveys. The participants in the standard-of-care arm will not receive any information about pay-it-forward.

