### Data Collection and Management

When participants are enrolled, the research assistants will record their enrollment time, envelope number, name, identification number, and group. Data will be collected on the professional Chinese questionnaire website Wenjuanxing [29] using self-designed questionnaires, including the baseline questionnaire (questionnaire A) and the follow-up questionnaires (questionnaires B and C). The information collected is presented in Table 2.

**Table 2 table2:** Summary of information to be collected.

Item	Questionnaire codes
Sociodemographics	A
Knowledge about PPSV-23^a^	A, B, and C
Dissemination of PPSV-23	A
Attitudes toward PPSV-23	A, B, and C
Gratitude (GQ-6^b^ scale)	A, B, and C
Willingness and reasons for receiving the PPSV-23	A
Feasibility, appropriateness, and acceptability of pay-it-forward (only pay-it-forward group)	A
Reasons for promoting or discouraging donations (only pay-it-forward group)	B and C
Incidence of adverse reactions or adverse events	B and C
Recommendation of PPSV-23 to others	B and C

^a^PPSV-23: 23-valent pneumococcal polysaccharide vaccine.

^b^GQ-6: Gratitude Questionnaire—6-item scale.

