### Statistical Analysis

#### Primary Outcome

Descriptive analysis will be used to summarize the sociodemographic characteristics, knowledge, attitudes, and behaviors of the participants in each arm. Cronbach α will be used to test the reliability of the scales in the questionnaire. For the primary analysis, we will conduct intention-to-treat and per-protocol analyses, using logistic regression to compare the odds ratios of vaccination rates between the pay-it-forward group and the standard-of-care group, with adjustment for sociodemographic characteristics (eg, sex, age, and education level). In addition, we will perform logistic regression analyses stratified by income level, chronic disease status, living status, and distance to the vaccination site.

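### Questionnaire A is labelled baseline but is given after allocation and after the intervention content, so its knowledge, attitude, gratitude and willingness scores are post-randomisation measurements

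*Protocol article*

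**What the plan says.** **Label.** Data Collection and Management describes the forms as "including the baseline questionnaire (questionnaire A) and the follow-up questionnaires (questionnaires B and C". Table 1 puts the baseline questionnaire in the week 0 (baseline) column.

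**Allocation.** Under Randomization, the study designer prepares opaque envelopes: "insert the intervention material and group assignment information, and seal them". The arm becomes known when the envelope is opened.

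**Pay-it-forward arm.** The vaccination leaflet is used first, "to introduce participants in the pay-it-forward group to" the disease and the vaccine. The program leaflet follows, "to explain the purpose of the program, access to the PPSV-23 vaccination subsidy (US $20.7". Participants are also told of "the donations made by previous pay-it-forward recipients, as well as the handwritten postcards containing encouraging messages for the PPSV-23 vaccination". The video comes next, and only then the form: "After watching the PPSV-23 promotional video, the participants will be surveyed by a research assistant using questionnaire A".

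**Standard-of-care arm.** These participants get the same vaccination leaflet and video, and no pay-it-forward information. After the video they are surveyed "using questionnaire A and informed that they will need to pay for the vaccination at the standard market price".

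**Content and use.** Table 2 collects knowledge, attitudes and GQ-6 gratitude at A, B and C, and willingness at A only. All four are secondary outcomes in Outcome Measures. The Primary Outcome analysis section states: "Descriptive analysis will be used to summarize the sociodemographic characteristics, knowledge, attitudes, and behaviors of the participants in each arm". The Secondary Outcomes section adjusts vaccine confidence for sociodemographic variables and compares the other secondary outcomes between arms. It allows last observation carried forward (LOCF) or multiple imputation for missing follow-up data.

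**The concern.** A baseline score is useful because it cannot have been influenced by treatment. Here the first measurement of knowledge, attitudes and gratitude follows both the shared education and the arm-specific content. A between-arm difference at A may already be a treatment effect.

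If the label is taken at face value, three uses follow naturally:

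- a baseline table, in which a real effect would look like imbalance;
- a change score, which would subtract the early effect;
- adjustment for A, which would remove part of it.

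A fourth route is in the plan itself. Under LOCF, a participant who misses both follow-up surveys would have a score taken just after the video entered as the week-4 value.

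At stake is the interpretation of the questionnaire-based secondary outcomes.

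**Working it through.** The plan gives no effect size, standard deviation or correlation for these scores, so there is no stated figure to reproduce. The timing question is settled by reading; the sizes below are illustrations.

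**1. Can A precede exposure?** No.
- Both Intervention subsections place A after the video.
- Table 2 lists feasibility, appropriateness and acceptability of pay-it-forward at A only, for that arm only. Those items presuppose that the program has been explained.
- Data Collection and Management says the two arms receive separate questionnaires, so the arm is known when A is given.
- No earlier measurement of these scores is described.

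**2. Which exposure can affect which comparison?** The leaflet and video reach both arms. They can raise both arms' scores at A and so hide a pre-to-post gain, but they do not by themselves create a difference between arms. Only the program explanation, the subsidy offer, and the earlier donations and postcards can shift the between-arm contrast at A.

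**3. Size if A is used as a baseline.** Let D be the true between-arm effect at follow-up, f the share of D already present at A, and ρ the within-arm correlation between A and follow-up (equal SDs, so that the slope equals ρ).
- Change from A shows D − fD = D(1 − f).
- Adjustment for A shows D − ρfD = D(1 − ρf).

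With D = 0.50 SD (assumed):

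| f | Change from A | Adjusted, ρ = 0.3 | ρ = 0.5 | ρ = 0.7 |
|---|---|---|---|---|
| 0 | 0.50 | 0.50 | 0.50 | 0.50 |
| 0.25 | 0.375 | 0.463 | 0.438 | 0.412 |
| 0.50 | 0.25 | 0.425 | 0.375 | 0.325 |
| 1 | 0 | 0.35 | 0.25 | 0.15 |

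If the shift is d at A and fades to d/2 by week 4, change from A shows d/2 − d = −d/2, which has the wrong sign.

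**4. Size under LOCF.** Suppose a share m of each arm misses both B and C, unrelated to the scores, and A is carried forward. The week-4 contrast becomes (1 − m)D + m·fD. Take m = 0.20, borrowing the dropout allowance in the Sample Size section, and D = 0.50 SD:
- f = 0.50: 0.80 × 0.50 + 0.20 × 0.25 = 0.45 SD.
- Effect at A twice that at week 4 (f = 2): 0.80 × 0.50 + 0.20 × 1.00 = 0.60 SD.

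So LOCF can err in either direction, depending on whether the effect grows or fades.

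**5. What is untouched?** Uptake comes from administrative records, and its model adjusts for sociodemographic characteristics. The economic evaluation measures effectiveness by vaccination uptake. Sociodemographic items in A are not plausibly altered by a leaflet or video.

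**The case against.** The strongest reply is that the harm in step 3 needs analyses the article does not plan. It states no change from A and no adjustment for A. A randomised comparison at B or C needs no baseline score and is not biased by when A was given. The sentence on descriptive summaries names no time point and no balance check. How repeated scores are modelled may be set out in an analysis plan that is not shown. All of this stands, and it makes the bias conditional.

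Several stronger readings are tempting but not supported:

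- **A follows donation and the participant's own postcard.** A reader might infer this from the row order in Table 1. That order is not chronological: it lists the pay-it-forward leaflet and the video before consent and allocation. The Intervention text asks about donating and writing a postcard at or after A.
- **The subsidy has been received before A.** It has only been explained; vaccination is scheduled afterwards.
- **The trial's explanatory question is lost.** The two stated hypotheses concern uptake and per capita cost, and no mediation analysis is described. The article mentions trust, confidence and knowledge as pathways but does not name gratitude as one.
- **The loss is total or reversed.** Those are the extreme cases in step 3. The GQ-6 is described as measuring a tendency, so f for gratitude could be small.

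What the reply does not remove is the mislabelling, the lack of any pre-intervention score, and the LOCF option, which is in the plan.

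**Conclusion.** The concern holds as a correction to the secondary outcomes. Questionnaire A is not a baseline for knowledge, attitudes or confidence, gratitude or willingness. This rests on the order given in the Intervention section and needs no assumption.

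The size of any bias is illustrative. With an assumed 0.50 SD effect of which half is present at A, change from A would show 0.25 SD, and adjustment for A would show 0.325 to 0.425 SD for ρ from 0.7 down to 0.3. If nothing is present at A, there is no bias by these routes. The bias arises only if A is used as a baseline or carried forward.

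A reader might infer that the trial's main conclusion is at risk. The documents do not support that: the primary outcome, its adjustment and the cost-effectiveness analysis do not use these scores.

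**What to change.** Recruitment has finished and results are still to come, so the change is to the analysis rules and the report:

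1. Relabel A as the immediate post-intervention (week 0) assessment.
2. Compare arms on knowledge, attitudes or confidence and GQ-6 at A, B and C as three post-randomisation time points, without subtracting or adjusting for A. Compare willingness at A, the only form for which Table 2 lists it.
3. Do not present A's scores as evidence of baseline balance.
4. Do not carry A forward as the week-2 or week-4 value.
5. Keep only A's sociodemographic items as baseline data and covariates.
6. State in the report that no pre-intervention scores were collected.

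This needs no new data or staff. The price is that within-arm change from a true baseline cannot be reported, and the precision that a baseline covariate might have brought is given up. If the design is reused, these items can be asked after consent and before the envelope is opened or any material is shown.

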#### Standard-of-Care Group

The participants in this group will also receive the same PPSV-23 vaccination leaflet, a promotional video, and a questionnaire (not including questions on pay-it-forward) similar to that provided to the pay-it-forward group. They will also be informed of the standard cost of the PPSV-23 vaccination (US $29.5-$30). After watching the PPSV-23 promotional video, the participants will be surveyed by a research assistant using questionnaire A and informed that they will need to pay for the vaccination at the standard market price. Participants who are willing to be vaccinated will be assessed for eligibility and scheduled for an appointment for vaccination. The CHW will also follow up with the participants in the second and fourth weeks after enrollment. The participants will receive 100 RMB (US $13.8) for completing the 3 surveys. The participants in the standard-of-care arm will not receive any information about pay-it-forward.

### Sample Size

The sample size was calculated using the PASS 2021 software after conducting a pilot trial. In the pilot trial, 88% (23/26) of the participants in the pay-it-forward group and 12% (3/26) of the participants in the standard-of-care group received the pneumonia vaccine. On the basis of the pilot trial results, we initially calculated the sample size to be 16. However, this sample size was determined to be too small to detect the desired effect size for the trial. To address this, we reviewed previous data on vaccination rates and estimated the expected difference in rates between the 2 groups based on prior experience. An earlier review indicated that the vaccination coverage of PPSV-23 among older adults in China ranged from approximately 1.23% to 42.10% [16]. Our previous pilot study showed that the pay-it-forward intervention increased influenza vaccination coverage in older adults by approximately 30% [23]. Considering these, we estimated a PPSV-23 vaccination coverage of 10% in older adults, and projected that the pay-it-forward intervention would increase this by 20%. The power of the test was set as 90% using a 2-sided test with a significance level of.05. The minimum sample size was calculated to be 158. After accounting for a 20% dropout rate, the minimum sample size required was adjusted to 198. The minimum sample size was further increased to 204 to accommodate the block-randomized design. Consequently, at least 204 participants were required for the trial.

### Data Collection and Management

When participants are enrolled, the research assistants will record their enrollment time, envelope number, name, identification number, and group. Data will be collected on the professional Chinese questionnaire website Wenjuanxing [29] using self-designed questionnaires, including the baseline questionnaire (questionnaire A) and the follow-up questionnaires (questionnaires B and C). The information collected is presented in Table 2.

**Table 2 table2:** Summary of information to be collected.

Item	Questionnaire codes
Sociodemographics	A
Knowledge about PPSV-23^a^	A, B, and C
Dissemination of PPSV-23	A
Attitudes toward PPSV-23	A, B, and C
Gratitude (GQ-6^b^ scale)	A, B, and C
Willingness and reasons for receiving the PPSV-23	A
Feasibility, appropriateness, and acceptability of pay-it-forward (only pay-it-forward group)	A
Reasons for promoting or discouraging donations (only pay-it-forward group)	B and C
Incidence of adverse reactions or adverse events	B and C
Recommendation of PPSV-23 to others	B and C

^a^PPSV-23: 23-valent pneumococcal polysaccharide vaccine.

^b^GQ-6: Gratitude Questionnaire—6-item scale.

We will collect the following information: (1) sociodemographic characteristics (eg, sex, marital status, education levels, monthly income, and employment); (2) knowledge of PPSV-23 (eg, age eligibility, reduced risk of hospitalization and death, and reduced medical costs owing to pneumonia); (3) attitudes toward PPSV-23, which will be evaluated using a standardized scale [30] to assess vaccination confidence among participants (eg, perceived safety, efficacy, and importance of the vaccine); (4) education and sensitization related to PPSV-23 (eg, recommendations from health care workers or friends); (5) tendency to show gratitude, which will be measured using the widely used Gratitude Questionnaire—6-item scale (GQ-6) [30]. (6) reasons for promoting or discouraging donations, which will be assessed among participants in the pay-it-forward group, along with the feasibility, appropriateness, and acceptability of the pay-it-forward interventions, using previously well-evaluated scales [31]. (7) incidence of adverse reactions (eg, fever, redness, swelling, pain, itching) or adverse events (eg, pneumonia, bronchitis, ear infections), which will be investigated for participants who receive vaccination; (8) reasons for declining vaccination, which will be collected from the participants who do not receive the vaccine; and (9) participants recommendations to others to receive PPSV-23.

The uptake of PPSV-23 will be verified using the immunization program’s information management system. Separate questionnaires will be administered to participants in the standard-of-care and pay-it-forward groups. Quality control questions have been included to ensure the accuracy of questionnaire completion. Two similar questions will be included in different sections of the questionnaire to assess the consistency of responses: (1) Does vaccination with PPSV-23 reduce hospitalization and deaths? and (2) Vaccination with PPSV-23 reduces hospitalization and death. If participants respond differently to these 2 similar questions, the questionnaire will be considered invalid, and they will be asked to complete it again. Once participants are enrolled, personally identifiable information and survey data will be entered into an electronic Microsoft Excel form. The form will be password-protected by the study designer, and only the study designer and the researcher responsible for data analysis will have access to it. A data safety and oversight committee will be established, comprising 2 clinicians, an epidemiologist and statistician, and a representative of the medical ethics committee, who will operate independently of the research team. The data safety and oversight committee will review the process of the study, data collection, data management, and analysis. Each participant will be assisted by a CHW in completing the survey. For older adults who do not have a smartphone, the survey will be completed using an electronic device provided by the research program, and the CHW will guide them through the QR code scanning and submission process.

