**Methods:**

A 2-arm, parallel randomized controlled trial will be conducted in 4 community health centers in Nanning city, Guangxi province, China. We will use a block randomization design. A total of 204 older adults will be randomly allocated in a 1:1 ratio to either the pay-it-forward group or the standard-of-care group. Each participant will complete a web-based questionnaire. The standard-of-care group will be required to pay for the vaccine themselves. In contrast, the pay-it-forward group will receive a 150 RMB (US $20.7) vaccination subsidy, postcards, and the opportunity to donate. The participants in both groups will be followed up in the second and fourth weeks after enrollment. The primary outcome will be uptake of the 23-valent pneumococcal polysaccharide vaccine, as determined by administrative data. Secondary outcomes include costs, pneumococcal vaccination knowledge, attitudes toward the vaccine, perceptions of gratitude, incidence of adverse reactions and adverse events, and the likelihood of recommending pneumococcal vaccination to others.

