### Outcome Measures

The primary outcome of this study will be the uptake of PPSV-23 in each arm, assessed 1 month after the intervention using administrative records. The secondary outcomes will include: (1) vaccine confidence, measured by 4 survey statements related to perceptions of the importance, safety, and efficacy of vaccination, as well as vaccine management; (2) influenza vaccination, defined as participants receiving the influenza vaccine after enrollment in the study, verified through administrative records, with the cost of the vaccination borne by the participants; (3) cost per person vaccinated and cost-effectiveness; (4) vaccine knowledge between the 2 groups; (5) attitudes toward vaccination; (6) willingness to vaccinate; (7) gratitude, measured by the GQ-6 scale; (8) the rate of successful vaccine referral, defined as participants successfully recommending PPSV-23 to others in the community after participating in the study; and (9) incidence of adverse events or reactions to vaccination.

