#### Secondary Outcomes

The economic evaluation will be conducted from a health care provider’s perspective with a 1-year time horizon. Microcosting methods will be used to evaluate the implementation costs of both the standard-of-care and pay-it-forward intervention groups. Specifically, we will collect cost data, including personnel time, medical supplies, equipment use, and facility expenses. Material procurement costs will be calculated using primary sources, such as invoices, while project implementation costs will be based on researchers’ self-reported data. Health care personnel’s time costs will be estimated using the local government–published wage standards. A decision tree model will be developed using TreeAge Pro 2022 software (TreeAge Software, LLC), with vaccination uptake (defined as the number of vaccinated individuals per intervention arm) serving as the effectiveness measure for the pay-it-forward intervention. The intervention will be compared against standard-of-care (participants’ self-paid PPSV-23 vaccination) to estimate incremental costs and incremental cost-effectiveness ratios. Model robustness will be assessed through 1-way sensitivity analyses and probabilistic sensitivity analysis. Influenza vaccination rates and vaccine confidence will be compared between the pay-it-forward intervention group and the standard-of-care group using logistic regression analyses, adjusted for sociodemographic information. Other secondary outcomes will be summarized using descriptive statistics and compared between the 2 arms.

Participants with missing primary outcome data (ie, vaccination status) will be reviewed. A complete case analysis will be performed if the proportion of missing primary outcome data is low (<5%). If the missing data exceed this threshold, multiple imputation methods will be applied under the assumption that the data are missing at random, to account for potential bias. Sensitivity analyses will also be conducted to assess the robustness of the findings under different assumptions about the missing data. To address missing follow-up data, we will use the last observation carried forward method or a multiple imputation method for missing values for categorical and continuous variables.

The results of all logistic regression analyses will be reported as crude odds ratios and adjusted odds ratios, along with 95% CIs. All statistical tests will be 2-sided, with a significance level of *P*<.05.

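### Adverse events are to be investigated in vaccinated participants yet compared between arms, a contrast that randomisation does not protect

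*Protocol article*

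**What the plan says.** Four places in the protocol article bear on this.

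- **Data Collection and Management, item 7.** Adverse reactions (such as fever or swelling) and adverse events (such as pneumonia, bronchitis or ear infections) are listed as information "which will be investigated for participants who receive vaccination". Item 8 deals separately with participants who are not vaccinated and collects their reasons for declining.
- **Outcome Measures, item 9.** The last secondary outcome is "incidence of adverse events or reactions to vaccination". No denominator and no time window after vaccination is given.
- **Statistical Analysis, Secondary Outcomes.** Specific analyses are named for the economic outcomes, influenza vaccination and vaccine confidence. For the rest: "Other secondary outcomes will be summarized using descriptive statistics and compared between the 2 arms". Adverse events fall under that sentence and nothing exempts them.
- **Pay-It-Forward Group.** "The CHWs will conduct follow-up surveys using questionnaire B and questionnaire C during the second and fourth weeks after enrollment". The Standard-of-Care Group section has the same timing. In both arms a willing participant is assessed for eligibility and then booked for vaccination.

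**The concern.** Read together, these sections restrict the adverse event data to vaccinated people and then compare the arms. Uptake happens after randomisation and is the primary outcome, and the trial is designed to show that it differs by arm. Conditioning on it gives up the balance that randomisation provides. Standard-of-care vaccinees are people willing to pay the full price. Pay-it-forward vaccinees include people who would not have been vaccinated without the intervention.

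Both arms are offered the same vaccine, so a between-arm difference in reactions has no clear reading as an effect of the subsidy and message. It could come from differences in age, health or readiness to report. The result could be an apparent safety signal, or reassurance, that the design cannot support. For general events such as pneumonia, the restriction also leaves out the unvaccinated participants who would be needed for a valid arm comparison.

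**Working it through.** **Inputs from the document**
- Sample Size: "we estimated a PPSV-23 vaccination coverage of 10% in older adults", and the authors "projected that the pay-it-forward intervention would increase this by 20" percent, read as percentage points, so 10% v 30%.
- Sample Size: "The power of the test was set as 90% using a 2-sided test with a significance level of.05"; 20% dropout; pilot uptake 3/26 (12%) v 23/26 (88%).
- Abstract, Methods: "A total of 204 older adults will be randomly allocated in a 1:1 ratio".
- Results: 220 enrolled.

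**Assumptions, not in the document**
- An equal split of the 220, that is 110 per arm.
- A common event rate of 20%, with 10% to 30% as the range. The document gives no event rate.

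**1. The plan's own sample size**

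Unpooled normal approximation, per arm: (1.960 + 1.282)² × (0.1×0.9 + 0.3×0.7) / 0.2² = 78.8, rounded up to 79, total 158. With dropout: 158 / 0.8 = 197.5, rounded up to 198. Both stated figures reproduce, which confirms that 10% v 30% is the intended reading.

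**2. Who contributes adverse event data**

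| Scenario (N = 220) | Standard of care | Pay-it-forward | Total |
|---|---|---|---|
| Planning rates | 110 × 0.10 = 11 | 110 × 0.30 = 33 | 44 |
| Pilot rates | 110 × 3/26 = 12.7 | 110 × 23/26 = 97.3 | 110 |

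At the planned 204 and the planning rates, the numbers are 10.2 v 30.6.

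**3. How far the subsets differ by construction**

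If uptake would be 10% under standard of care and 30% under pay-it-forward, at least 30 − 10 = 20 of every 30 pay-it-forward vaccinees (two thirds) are, in expectation, people who would not have been vaccinated in the other arm. At the pilot rates the fraction is at least (23 − 3)/23 = 87%. This says nothing about whether their event risk differs. It shows only that the two groups are not comparable by design.

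**4. Precision of the arm contrast**

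Half-width of the 95% CI for the difference: 1.96 × √[p(1 − p)(1/n₁ + 1/n₂)].

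| Event rate p | 11 v 33 | 13 v 97 |
|---|---|---|
| 10% | 20 points | 17 points |
| 20% | 27 points | 23 points |
| 30% | 31 points | 27 points |

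At 20%: 1.96 × √[0.16 × (1/11 + 1/33)] = 0.273, and 1.96 × √[0.16 × (1/13 + 1/97)] = 0.232. The extra pay-it-forward vaccinees in the pilot scenario help little, because the small standard-of-care subset is the limit. The normal approximation is rough here (11 × 0.20 = 2.2 expected events in the smaller group), so these are orders of size.

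**5. Precision of the pooled rate**

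With 44 vaccinees and p = 20%: 1.96 × √(0.16/44) = 0.118, about 12 points. This is a single rate, not a difference, so it answers another question: how often vaccinees in this trial report a reaction.

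**6. Observation time**

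Surveys run at weeks 2 and 4 from enrollment, and vaccination follows by appointment. Someone vaccinated shortly before week 4 has almost no time in which an event could be recorded. Time at risk therefore varies between individuals.

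**The case against.** The best defence is that the analysis sentence names no test, model or denominator for adverse events. A simple table of reactions by arm would satisfy it, and the choice of safety population is often left to a fuller document. Table 2 also lists adverse reactions and events under questionnaires B and C with no restriction to vaccinees, although it marks two other items as limited to the pay-it-forward group. The questions may therefore have gone to everyone. The outcome is the last of nine, neither hypothesis concerns safety, and the primary analysis does not depend on it.

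Part of this stands. The impact is limited, and whether unvaccinated participants were asked needs to be checked. It does not remove the point. The restriction in item 7 is explicit, and item 8 treats the unvaccinated separately. A between-arm comparison is also stated, so this is a rule as written and not an omission.

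Some stronger readings are tempting but unsupported:
- **Observation time differs between the arms.** The survey schedule and booking process are the same in both. Only variation between individuals follows from the text.
- **The contrast will be 11 v 33.** That is one scenario; the pilot rates give about 13 v 97.
- **Selection will produce a false signal of a given size.** That needs separate event rates for full-price payers and for people moved by the intervention, and the document gives none. Pay-it-forward vaccinees also still pay part of the price: the subsidy is US $20.7 against US $29.5 to $30.

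**Conclusion.** The point holds. As written, the plan compares adverse events between subsets defined by the primary outcome, so an arm difference cannot be attributed to the intervention. That conclusion needs no assumed event rate.

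The contrast is also imprecise: about 27 points either way at the planning uptake and 23 at the pilot uptake, given an equal split of the 220 and a common 20% event rate. Over event rates of 10% to 30% and both uptake scenarios, the half-width runs from 17 to 31 points.

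This should be corrected, but it does not threaten the trial. One secondary outcome is affected.

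**What to change.** In Statistical Analysis, Secondary Outcomes:

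1. Exempt adverse events and reactions from the between-arm comparison.
2. Report reactions per vaccinated participant, pooled over arms, with exact CIs and no arm test. By-arm counts may be shown as description only.
3. Show days observed since vaccination where the vaccination date is available. The document says that the immunization information system confirms uptake. It does not say that dates will be extracted, so this should be checked before it is promised.
4. Compare general adverse events such as pneumonia by arm only if questionnaires B and C recorded them in all randomised participants; otherwise list them. Align item 7 of Data Collection and Management and Table 2 with what was done.

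Steps 1 and 2 are changes of wording. Step 3 may need a data request, and step 4 a look at the questionnaires used. Recruitment is complete, but final results are expected only in June 2026, so the change can be documented before they are reported. What is lost is a between-arm p-value that carries little information.
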